## Abstract

**Background:**

The management of breakthrough pain in cancer patients is always a challenge for medical professions. Occurring in 80% of cancer patients with advanced disease, breakthrough pain significantly decreases both patient’s and caregiver’s quality of life. The aim of this study is to assess the analgesic efficacy of a fixed inhaled nitrous oxide/oxygen mixture for adult cancer patients with breakthrough pain.

**Methods/design:**

This is a randomized, placebo-controlled, double-blind study; it will be conducted in the General Hospital of Ningxia Medical University. The target study subjects are at least 18 years old, and are hospitalized cancer patients who are receiving routine opioids to control cancer-related pain but still experience breakthrough pain. A total of 240 patients will be recruited and randomly allocated between three treatment groups (A, B, C) and a control group (group D) in a ratio of 3:1. All treatment groups (A, B, C) will receive standard pain treatment (oral immediate-release morphine) plus a pre-prepared nitrous oxide/oxygen mixture, and the control group (D) will receive the standard pain treatment plus oxygen. Patients, doctors, nurses, and data collectors are all blind to the experiment. Assessments will be taken before treatment (T0), at 5 min (T1) and 15 min (T2) during treatment, and at 5 min after treatment (T3). The primary endpoint measures will be the percentage of patients whose pain is relieved at T1, T2, and T3. Secondary outcome measures will include the safety of treatment, adverse events, and satisfaction from both health professionals and patients.

**Discussion:**

This study aims to provide an effective and practical intervention for a fast breakthrough pain relief and to improve cancer patients’ quality of life significantly. The Evidence-Based Medicine Working Group claim that a randomized, double-blind, placebo-controlled experimental intervention is the most appropriate design to demonstrate its efficacy, so this study could give a new approach to controlling breakthrough pain episodes.

**Trial registration:**

ChiCTR-INC-16008075. Registered on 8 March 2016.

**Electronic supplementary material:**

The online version of this article (doi:10.1186/s13063-016-1739-9) contains supplementary material, which is available to authorized users.

## Background

In 2015, there were approximately 15 million newly diagnosed cancer cases in the world and about 4.3 million new cases in China alone [1, 2]. Cancer pain is common. The estimated prevalence of cancer-related pain is 30–50% for those who are under chronic pain treatment; over 80% of those with advanced disease suffer moderate to severe pain [3]. Most cancer pain is chronic and caused by the tumor. About 50–90% of patients reported intermittent flaring of pain [4] with a 30–40% rate during the early stages of the disease and 70–90% during advanced stages [5].

Cancer pain is classified as background pain or breakthrough pain according to its temporal characteristics [6, 7]. Background pain, also known as chronic persistent pain, refers to a constant or continuous pain that lasts for more than 12 hours per day [6]. Breakthrough pain is a negative prognostic indicator for pain control. The Association for Palliative Medicine of Great Britain and Ireland task group defines breakthrough pain as a transitory increase in pain intensity that occurs either spontaneously or in relation to a specific predictable or unpredictable trigger despite the use of long-term and around-the-clock analgesics to control background pain. With this definition, breakthrough pain includes both spontaneous (idiopathic) and incidental (precipitated) pain. Spontaneous pain is unpredictable. Incidental pain is somewhat predictable and usually categorized into three sub-types: volitional, non-volitional, and procedural [6–13]. More than 50% of breakthrough pain is reported to be spontaneous [13].

Both inter-individual and intra-individual breakthrough pain varies in terms of timing and severity [6]. A typical breakthrough pain episode is characterized by a rapid onset (median interval of 3 min to peak pain) [14], moderate to severe in intensity (numerical pain rating scale > 4), short duration (median 30–60 minutes) [14], and self-limited (median number of 4 (times) episodes per day with a range of 1-14) [8, 15]. Patients with breakthrough pain have significantly greater pain-related functional impairment [3, 16] and decreased satisfaction with their analgesic therapy [6]; these are correlated with increased suicidal thoughts [17]. The unrelieved breakthrough pain increases patients’ psychological distress and susceptibility to such illnesses as depression and anxiety [3, 18], which put a negative impact on quality of life [3, 6, 19]. It also lays an additional economic burden on the healthcare system because it increases emergency outpatient visits, hospital admissions, and hospital stay [20–22].

The World Health Organization three-step analgesia ladder can manage about 80% of background pain with simple interventions [5, 15]. However, the sudden onset, severity, and short duration of breakthrough pain make its management more difficult [15]. Traditionally, breakthrough pain is managed by varying oral immediate-release opioid at 5–15% [23], 10–20% [24], or one-sixth of the total daily opioid dosage [14]. However, in most cases, the pharmacokinetic and pharmacodynamic profiles of such oral opioids do not align with the rapid nature of breakthrough pain [25–27]. Several studies indicated that the average onset of action for oral opioid (including morphine, oxycodone, and hydromorphone) as rescue medications among hospice patients was greater than 30 min [28, 29]. This long onset of action means that the oral immediate-release opioids are not ideal rescue medications for most breakthrough pain. Studies have evaluated the effectiveness of transmucosal fentanyl formulations for breakthrough pain management [29]. As oral or nasal mucosa allows a more rapid absorption and avoids the first-pass metabolism, transmucosal fentanyl’s onset of action is within 10–15 min after administration [29, 30]. However, some research suggested that the oral transmucosal fentanyl citrate showed a negative correlation with a fixed-schedule opioid regimen and patients have to undergo up to 26 days of the dose-titration phase to determine the optimal dose [31, 32]. Another drawback for this preparation is its high cost. Intravenous morphine is another agent that, at 20% of its basal oral dosage, is a fast, safe, and highly effective option for the relief of breakthrough pain. Its onset of action starts in 3 min and peaks at 10 min [33], but this invasive route of administration and the lack of breakthrough pain management guidelines made this approach less favorable.

A self-administered inhaled nitrous oxide/oxygen mixture is available in pre-prepared cylinders. It has been used in various types of pain management, including labor [34], dental procedures [35], trauma [36], burn dressing [37], surgical procedures, and other medical conditions. The nitrous oxide/oxygen mixture has potent analgesic properties but does not cause loss of consciousness. This gas is safe, noninvasive, and an effective form of pain relief, owing to its low blood/gas solubility ratio, which allows for rapid onset (1–2 min) and short duration of action (35–45 s) after discontinuation [38, 39]. The absorbed gas is also readily excreted unchanged mainly through the lungs [40, 41]. The administration of nitrous oxide/oxygen mixture is easy to control. Its side effects is generally disappear quickly after the termination of exposure to the gas [40, 41].

In mainland China, transmucosal fentanyl preparations are not available and have not been used to control breakthrough pain [data from Chinese Marketed Drugs Database]. According to anesthetists, oral immediate-release opioid is the first choice in controlling breakthrough pain in China. However, with its slow onset of action (20–30 min; peak > 45 min) [42], it delays pain relief and reduces patients’ compliance. Studies by Li et al. showed that a fixed diluted nitrous oxide/oxygen mixture would provide a sufficient analgesic effect during the burn-dressing procedure; patients reported the most satisfaction for this method [17, 37]. However, to our knowledge, there are no studies on the use of nitrous oxide/oxygen mixture to treat breakthrough pain yet. We hypothesize that a nitrous oxide/oxygen mixture can provide the same analgesic effect for cancer patients within breakthrough pain episodes. This is a nurse-led, patient-participate, randomized controlled trial. This article describes the study background, design, treatment administration, and data analysis approach.

## Methods

### Study design

This study is a randomized, double-blind, placebo-controlled, parallel clinical trial to test the analgesic efficacy of a fixed inhaled nitrous oxide/oxygen mixture on adult cancer patients with breakthrough pain. This article has been drafted following SPIRIT guidelines [43] (see Additional file 1). Patients in the treatment groups will receive standard pain treatment plus pre-prepared nitrous oxide/oxygen mixture and patients in the control group will receive standard pain treatment plus oxygen when they report a breakthrough pain episode. The study protocol will use the Consolidated Standards of Reporting Trials (CONSORT) [44] statement recommendations (see Additional file 2). The overall trial design is provided in Fig. 1. Furthermore, the schedule of enrolment, interventions, and assessments are presented in Table 1. The stratification factors were not contemplated in this study. breakthrough pain is a transitory exacerbation of pain that occurs despite the use of long-term and around-the-clock analgesics to control persistent pain, and there is no nature differences in two types of breakthrough pain. So we did not make stratification analyses in this study.

**Fig. 1 Fig1:**
[figure not shown]
Study design framework. BP, blood pressure; BTP, breakthrough pain; HR, heart rate; NOOM, nitrous oxide/oxygen mixture: NRS, numerical pain rating scale; SPO_2_, oxygen saturation; STN, standard treatment with nitrous oxide/oxygen mixture; STO, standard treatment with oxygen

**Table 1 Tab1:** Schedule of enrolment, interventions, and assessments

	Study period				
	Enrolment	Post-allocation			Close-out
Timepoint	Diagnosed with breakthrough pain	Breakthrough pain episode (T0)	5 min after starting intervention (T1)	15 min after starting intervention (T2)	5 min after finishing intervention (T3)
Enrolment					
Eligibility screen	√				
Informed consent	√				
Allocation	√				
Interventions					
Control group			√	√	
Treatment groups			√	√	
Assessments					
Numerical pain rating scale		√	√	√	√
Blood pressure		√	√	√	√
Oxygen saturation		√	√	√	√
Heart rate		√	√	√	√
Satisfaction					√
Side effect			√	√	√

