### Treatments

Eligible patients will receive oral immediate-release morphine with a proportion of 10–20% daily total doses of oral morphine as the standard breakthrough pain treatment [24]. Patients will be instructed to use of study apparatus, which provides a fix concentration of nitrous oxide/oxygen mixture or oxygen to a disposable, demand valve, scented oral–nasal mask. Patients will hold the mask, which is opened by the negative pressure of patients to control the gas taken in. The experimental group will receive a fixed concentration of nitrous oxide/oxygen mixture and the control group will receive oxygen during breakthrough pain episodes. Gas inhalation will be administered until the breakthrough pain episode is over. The project manager is in charge of assignment, allocation, and treatment delivery. All gas cylinders used in both two groups are identical in appearance. The patients, nurse, and data collector are all blind to the treatment.

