### Measurement

Patient’s demographic data (age, sex, nationality, height, weight), cancer diagnosis, baseline breakthrough pain intensity, current background pain opioid medication dosage, duration of nitrous oxide/oxygen mixture use, dosage of oral rescue morphine medication, and any side or adverse effects of nitrous oxide/oxygen mixture treatment will be recorded by researchers [45]. A numerical pain rating scale (range from 0 to 10) is used to assess for pain intensity along with heart rate, noninvasive monitoring of blood pressure, and digitally monitored oxygen saturation at baseline (T0 before treatment), 5 min (T1) and 15 min (T2) after the beginning of treatment, and at 5 min (T3) after treatment finished. Heart rate, blood pressure, and oxygen saturation will be monitored by Infinity® Delta XL (Draeger Medial Systems Inc., Danvers, Shanghai, China). A five-point satisfaction scale (5, very satisfied; 4, satisfied; 3, uncertain; 2, dissatisfied; 1, very dissatisfied) will be used to assess both patients’ and healthcare professionals’ satisfaction with breakthrough pain treatment [46]. Any side effects of the nitrous oxide/oxygen mixture treatment, such as nausea, vomiting, dizziness, drowsiness, and headache [17], will be carefully monitored by researchers after the initiation of the gases inhalation.

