#### Secondary endpoint measures

Secondary outcome measures will include treatment safety, adverse events, and satisfaction from both health professionals and patients. The total time of nitrous oxide/oxygen mixture administration will be also recorded.

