### Data management and analysis

Before the study, all data collectors will be trained in the data collection procedure. Data from withdrawn patients will not be used in the final analysis. SPSS version 22.0 (SPSS Inc., IBM Company, Chicago, IL, USA) will be used to conduct quantitative analysis following the intention-to-treat principle for a case-control randomized trial. Descriptive statistics will be analyzed by medians (inter-quartile ranges), means (standard deviations), and proportions (exact binomial 95% confidence intervals), as appropriate. Proportions will be compared by using the chi squared test or the Fisher’s exact test. Means will be compared using Student’s *t* test (normal distribution parameters) or a nonparametric two-sample Mann–Whitney test (non-normal distribution parameters). Statistical significance will be considered for *P* < 0.05.

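### The last scheduled side-effect record is tied to the end of gas, so a crude comparison up to T3 would favour the mixture for background and morphine-related events if it shortens episodes

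*Protocol article*

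**What the plan says.** - **Schedule.** Table 1 ticks side effects at T1 (5 min), T2 (15 min) and T3. T3 is the close-out column, headed "5 min after finishing intervention (T3". The Measurement section gives the same definition: "at 5 min (T3) after treatment finished".
- **End of gas.** Treatments: "Gas inhalation will be administered until the breakthrough pain episode is over". This applies to both the mixture and oxygen.
- **Monitoring.** The Measurement section says side effects "will be carefully monitored by researchers after the initiation of the gases inhalation". It names a start and no end.
- **Outcome.** "Secondary outcome measures will include treatment safety, adverse events, and satisfaction from both health professionals and patients".
- **Exposure time.** Secondary endpoint measures: "The total time of nitrous oxide/oxygen mixture administration will be also recorded". The Measurement section also lists duration of use for the mixture. Neither section mentions oxygen.
- **Test.** Data management and analysis: "Proportions will be compared by using the chi squared test or the Fisher’s exact test". Exposure or observation time is not mentioned.
- **Morphine.** Every patient takes oral immediate-release morphine. The Background describes oral immediate-release opioid "with its slow onset of action (20–30 min; peak > 45 min" in the same unit.

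**The concern.** T1 and T2 are at fixed clock times from the start of gas, the same in every group. T3 is not: it moves with the end of the episode, which the mixture is meant to bring forward. The length of scheduled side-effect observation is therefore itself a consequence of treatment.

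This matters most for events that the gas does not cause. The listed effects (nausea, vomiting, dizziness, drowsiness, headache) can also come from the opioid or the disease. A patient whose episode ends at 15 to 20 min reaches T3 at 20 to 25 min, at about the time the article says oral opioid starts to act. A control patient with a 45 to 60 min episode is still being assessed at or after its peak. A crude count up to T3 would then show fewer such events with the mixture, even where the underlying rates are equal. It could also mask part of a real excess. Safety and adverse events are named secondary outcomes, so the comparison will be read.

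**Working it through.** The plan gives no figure for the safety window, so there is none to reproduce. The check asks how far unequal windows alone could move a crude comparison.

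**Inputs from the article**
- Scheduled window = gas time + 5 min (Table 1, Treatments). T2 also falls at 15 min, so 15 min is the minimum.
- Episode length: median 30–60 min (Background).
- Patients: 180 in the three treatment groups, 60 control (Randomization section).

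**Assumptions, not in the article**
- The same constant hazard h in both arms, set by a 60-min risk r: h = −ln(1 − r)/60.
- Gas times of 20 min (mixture) and 45 min (control), giving windows of 25 and 50 min.

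**Expected proportions**, P = 1 − exp(−h × window). For r = 20%, h = −ln(0.8)/60 = 0.00372 per min.
- Mixture: 1 − exp(−0.00372 × 25) = 8.9%
- Control: 1 − exp(−0.00372 × 50) = 17.0%
- Risk ratio: 8.9/17.0 = 0.52, with no true difference in rate.

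**False-significance rate.** Two-sided 5% chi squared test without continuity correction, summed exactly over both binomial distributions at 180:60:

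| 60-min risk | 25 vs 50 min | 35 vs 50 min |
|---|---|---|
| 2% | 9% | 6% |
| 5% | 17% | 10% |
| 10% | 27% | 13% |
| 20% | 43% | 17% |

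Nearly all of these false findings favour the mixture. With equal 50-min windows the rate is about 3% at a 2% risk and about 5% at the other three risks. In an extreme case (20 vs 65 min, 40% risk) it reaches 99%.

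**Masking of a real excess** (r = 20%)
- If the mixture doubles the hazard throughout: 1 − exp(−2 × 0.00372 × 25) = 17.0%, against 17.0% in control. Equal 50-min windows would show 31% vs 17%.
- If the gas instead causes early effects in 20% of patients on top of the same background hazard: 1 − 0.8 × exp(−0.00372 × 25) = 27% vs 17%. Equal windows would show 34% vs 17%. The excess is reduced but still visible.

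**What a 0–15 min comparison alone would cost** (r = 20%)
- Control: 1 − exp(−0.00372 × 15) = 5.4%, about 3 of 60 patients.
- Doubled hazard in the mixture groups: 10.6%.
- Power at 180:60 is about 19%.

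**The case against.** A reader might infer that side effects are counted only until T3 and that the safety result is therefore biased. The article does not say that. Its monitoring sentence has no end time, Table 1 lists scheduled assessments and not an adverse-event cut-off, and no endpoint of any event up to T3 is defined. The rule for proportions is generic, and pooling of time points could be left to an analysis plan. This stands, and it limits the point to what a crude comparison up to T3 would do. It does not remove the point: no later assessment is scheduled, and no other method for proportions is named.

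It can also be said that fewer side effects after less gas is a benefit of treatment. That is right for gas-specific effects. The Background says they generally fade quickly once gas stops, so a window of exposure plus 5 min suits them. The bias concerns background and morphine-related events.

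The wording on gas time may simply mean study gas, since blinded collectors could hardly time one arm only. That is likely. It makes the correction a matter of wording, but any adjustment depends on having the time for everyone.

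Finally, the windows and risks are assumed. The 90% versus 10% in the sample size section refers to a 30% fall in pain at 15 min, not to the end of the episode, so it does not supply gas times. A constant hazard is also a simplification where gas effects come early and morphine effects late. The 43% is thus one illustration and not an estimate for this trial.

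**Conclusion.** The point holds in a conditional form. As written, the length of scheduled side-effect observation depends on response. If the mixture shortens episodes, a crude comparison up to T3 would favour it for background and oral-morphine-related events. If gas times turn out equal in the arms, there is no bias.

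The size cannot be derived from the document. Under an equal constant hazard and windows of 25 versus 50 min, false significance runs from about 9% at a 60-min risk of 2% to 43% at 20%. It is lower where the windows are closer. The document does not support the stronger statements that recording stops at T3, or that a real harm would disappear. The second holds only for a particular pairing of hazard and window. This is a clarification worth making to a secondary safety analysis, and it is best made before data collection.

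**What to change.** 1. In Measurement and Secondary endpoint measures, replace the reference to time on the mixture with total study-gas time, recorded in all four groups under the blind. Record the side-effect observation time for each patient as well.
2. Compare side-effect proportions between arms at T1 and T2, which are fixed from the start of gas and already scheduled.
3. Report events through T3 as rates per observed time, and do not rely on the crude T3 proportion alone.

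**Cost.** A form label, one extra time field and a few lines of analysis text. The T1 and T2 comparison covers only 0–15 min, has few events (about 19% power for a doubled rate under the 20% assumption) and ends before the morphine onset of 20–30 min. It should stand beside the time-adjusted comparison and not replace it. The rates per observed time are themselves easiest to read when the hazard is roughly steady, which is a further reason to show both. No change to treatment or clinical monitoring is proposed.

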### Participants

All cancer patients from the oncology ward who have breakthrough pain will be invited to participate. Davies’ Adapted Diagnostic Algorithm will be used to screen patients for the presence of breakthrough pain [8]. The main inclusion criteria are: Chinese-speaking patients older than 18 years; recent worst pain (breakthrough pain) reported to be 4 or higher on a numerical pain rating scale of 0 to 10; a score on the Karnofsky Performance Status Scale above 20; and ability to take deep breaths in order to use the self-administered device. Patients will be excluded if they have a known contraindication to the use of nitrous oxide or have impaired cognitive function. Specific inclusion and exclusion criteria are presented in Table 2.

**Table 2 Tab2:** Inclusion and exclusion criteria

Inclusion criteria
Patient aged 18 years or older
Patient experiencing breakthrough pain episode with a stable dose of opioids to control background pain
Written informed consent for participation obtained prior to any study procedures
Exclusion criteria
Patient with mental disorder, altered mental status
Patient has difficulty in reporting pain
Karnofsky Performance Status Scale score under 20
Abdominal distension or suspected bowel obstruction, air embolism, pneumothorax, decompression sickness, epilepsy, pulmonary cancer, chronic obstructive pulmonary disease and acute respiratory infection, pregnancy, severe inhalation injury; pharmaceutical or pathological pulmonary fibrosis; maxillofacial injuries
Disease involving ear, nose, larynges, such as sinuses, middle ear

